### Statistical analysis

This pilot study intends to examine the confidence interval estimation and feasibility of the presented approach (physical activity and probiotic supplementation) [49, 50]. Attendance and retention rates will be assessed to calculate adherence. Attendance rate will be analysed by dividing the mean value for the number of participants present by the number of sessions offered during the four-week exercise period and the four-week probiotic intervention. The retention rate will be analysed by the percentage of participants completing all sessions of the endurance training (twelve in total), shuttle run test (two in total), nutrition questionnaire (four in total), blood/saliva measurement (four in total) and stool diagnostics (four in total) present in each step of the study. A retention rate of > 80% will be considered as feasible to conduct a future randomised controlled trial. Hypothesis testing and results of regression modelling will be considered entirely exploratory in nature and interpreted with caution. Our trial is mainly conducted in preparation for a future definitive randomised controlled trial to assess the efficacy of the intervention/study design [51]. All data will be entered into the database management software and analysed by the SPSS Version 25.0 (SPSS Inc., Chicago, IL, USA). The Shapiro-Wilk test will be used for variable normal distribution and the usual descriptive statistics for background information and mean values with a 95% confidence interval. Data will be used for sample size estimation and to determine the most appropriate outcome measure for the main study. Descriptive statistics and confidence intervals will also be calculated to examine the trends in the analysed parameters. This information will help to identify which parameters to focus on in future trials. Depending on the normality of the underlying data, parametric or non-parametric (e.g. unpaired *t* test/Mann-Whitney *U* test) tests will be carried out. Furthermore, a paired *t* test/Wilcoxon test might be computed for the longitudinal comparison (T0–T3). Bivariate correlation analyses might be assessed by the Spearman/Pearson correlation coefficient. Multivariate analyses with linear or logistic regressions might be performed to explore potential effects of the intervention and further potential covariates and cofactors. Moreover, multiple regression models might be used if multiple variables are predictive. The level of statistical significance is *p* < 0.05.

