### Aims and objectives

Primary outcomes of this randomised, controlled, cross-over pilot trial are the feasibility and practicality of the intervention, the validity of the study design and the provision of a reliable estimate for sample size calculation. To assess the practicality of the intervention, the duration (60 min), frequency (three times per week) and intensity (70–80% HRpeak) of the exercise programme will be considered as well as the adherence to the daily probiotic supplementation. The validity of the study design will be assessed with regard to the collection and immediate shipping of faecal samples. A further assessment will be made considering the time commitment for participants to complete endurance training, anthropometric testing, faecal samples and food diaries. In order to evaluate the efficacy of the intervention, the influence of moderate endurance training compared to probiotic supplementation (SymbioLactComp®) on the intestinal microbiota composition and barrier function (selected mucosal and immune parameters) as well as on selected blood and saliva biomarkers (haemogram, selected cytokines) in healthy student athletes will be examined.

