#### Exercise intervention

Exercise intensity will be calculated based on the HRpeak determined during a shuttle run test performed at the outset of the study. The training goal is a 10-km run in 50 min (males) or 55 min (female). The intensity of exercises will increase from 70% to 85% of the HRpeak to improve the subject’s basic endurance [39]. The three 60-min running sessions per week will consist of extensive and intensive continuous methods, interval training and stretching [39]. The exercises will be performed in groups and supervised by a sports scientist. Ratings of perceived exertion will be checked using a Borg Scale; the heart rate will be measured using a pulse monitor and belt from Polar® (Polar® Typ FT1). Participants will keep a training diary to log the completion of exercises. A training plan is shown in more detail in the appendix (see Additional file 3).

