#### Probiotic intervention

The probiotic period involves supplementation with the probiotic SymbioLactComp® (SymbioPharm GmbH, Herborn, Germany). SymbioLactComp® contains different lactic acid bacteria (*Lactobacillus paracasei*, *Lactobacillus acidophilus*, *Lactococcus lactis* and *Bifidobacterium animalis* subsp. *lactis*) as well as 30 μg of biotin. The total bacteria count of one sachet (2 g) is ≥ 1 × 10^9^ KBE/g. One sachet will be mixed with water and taken daily at breakfast.

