### Sample size

It is estimated that a sample size of a minimum of 30 participants is required in order to provide a pooled standard deviation that provides enough precision for the development of a future trial [46, 47].

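### The attendance rate divides people by sessions, so it is not a proportion, and neither stated adherence rate measures probiotic intake

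*Protocol article*

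**What the plan says.** The Statistical analysis section of the protocol article introduces two rates for one purpose: "Attendance and retention rates will be assessed to calculate adherence". It defines the first as follows: "Attendance rate will be analysed by dividing the mean value for the number of participants present by the number of sessions offered", and applies it "during the four-week exercise period and the four-week probiotic intervention".

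The second, retention, is a percentage of participants. It is based on "completing all sessions of the endurance training (twelve in total") and on the shuttle run tests, nutrition questionnaires, blood and saliva measurements and stool samples. Sachet intake is not in that list. A threshold above 80% is attached to retention; a similar one is attached to recruitment under Participants and recruitment. None is attached to attendance.

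Aims and objectives makes feasibility and practicality primary. Practicality is to be judged on the duration, frequency and intensity of the exercise, "as well as the adherence to the daily probiotic supplementation". The Probiotic intervention section describes that supplementation only as a home routine: "One sachet will be mixed with water and taken daily at breakfast".

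**The concern.** An attendance rate needs the number of people expected in its denominator. The stated formula has only the number of sessions, so its value rises with the number enrolled and falls when more sessions are offered, even if everyone behaves identically. A figure of that kind cannot be read as adherence, compared between groups of different size, or carried over to the larger trial that this pilot is meant to prepare.

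The second difficulty is scope. The same sentence covers the probiotic weeks, but the article describes no probiotic session that anyone could attend. Because retention does not count sachets either, a participant who took none could still be counted as fully retained. For a pilot with practicality among its primary outcomes, one of the two interventions would have no stated adherence rate.

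**Working it through.** **Inputs**
- Participants: "a sample size of a minimum of 30 participants is required" (Sample size), so n = 30.
- Allocation: 1:1 to the two sequences (Randomisation), so about 30 / 2 = 15 exercise together in a period.
- Sessions: "The three 60-min running sessions per week will consist of extensive and intensive continuous methods, interval training and stretching" (Exercise intervention), over four weeks.
- Probiotic: one sachet daily for four weeks; no sessions described.

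**The plan's own figure.** 3 sessions × 4 weeks = 12, which agrees with the twelve given in the retention definition.

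**Formulas.** Let a be the true attendance proportion, n the number expected at each session and S the number of sessions offered.
- As written: (mean present) / S = a × n / S.
- As a proportion: person-sessions attended / (n × S) = (a × n × S) / (n × S) = a.

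The two differ by the factor n / S. They agree only when the number expected happens to equal the number of sessions.

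**Exercise period, S = 12**

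| Expected per session | True attendance | As written | Proper rate |
|---|---|---|---|
| 15 (one sequence) | 100% | 15/12 = 125% | 100% |
| 15 (one sequence) | 80% | 12/12 = 100% | 80% |
| 30 (sequences pooled) | 100% | 30/12 = 250% | 100% |
| 30 (sequences pooled) | 80% | 24/12 = 200% | 80% |

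The one-sequence rows fit the cross-over better, since only about half the participants exercise at any one time. The pooled rows add the two sequences' attendance over a single set of 12 sessions. If instead the sessions run for both sequences are all counted (12 + 12 = 24), full attendance gives 15/24 = 62.5%. The choice of reading alone moves full attendance from 62.5% to 250%.

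**Check of the pooled 80% case.** 0.8 × 30 × 12 = 288 person-sessions; 288 / (30 × 12) = 288/360 = 80%.

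**Probiotic period.** With no sessions, the denominator is zero and the ratio is undefined. If each daily dose is assumed to count as a session, there are 7 × 4 = 28. Full adherence then gives 15/28 = 54% or 30/28 = 107% for that period alone, and 15/40 = 37.5% or 30/40 = 75% with the 12 exercise sessions added. None of these is 100%.

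**The case against.** The best defence is that the intent is plain: mean sessions attended per participant, divided by sessions offered. That may well be what was meant for exercise, and it would be a valid rate, but the text specifies participants present. It also does nothing for the probiotic weeks.

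Several limits on the point do stand:
- **The data for exercise exist.** Sessions are held in groups under supervision and participants log them in a training diary (Exercise intervention). A reader might infer that a primary feasibility measure cannot be obtained at all. The documents do not support that: only the formula fails, and a corrected denominator recovers the rate.
- **250% is not the natural headline.** A reader might take 30/12 as the expected value. In this cross-over about 15 exercise per period, so 125% is the better illustration and 250% needs both sequences pooled over one set of sessions.
- **The progression thresholds are untouched.** The 80% criteria belong to recruitment and retention. A reader might infer that the decision to proceed is computed from a faulty number; it is not. Retention also gives exercise adherence a second measure, through completion of all twelve sessions.
- **Some supplement intake is recorded.** The food diaries (Nutritional data) ask for nutritional supplements. Each lasts 7 days, so if one falls in the probiotic period it covers at most 7 of 28 days, or 25%, and the article does not link it to adherence.

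An article may also leave the method of recording sachets to the full protocol, so the absence of that detail is not the point. The point is that the rate the article does state for the probiotic period does not fit it.

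**Conclusion.** The concern holds in a limited form. The attendance definition is wrong as written, not merely brief: followed literally, it gives 125% for full attendance and 100% for a true 80% in a sequence of 15. These figures rest on 30 participants split evenly and on 12 sessions; with other numbers the error is the factor n / S. Probiotic adherence, part of the primary practicality outcome, is measured by neither stated rate. No progression criterion is computed from the formula, and exercise attendance is recoverable at analysis. The probiotic side is more pressing, because full intake cannot be reconstructed afterwards if it was not recorded during those weeks.

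**What to change.** Replace the attendance sentence with two definitions, both in all randomised participants:
- Exercise attendance = person-sessions attended / (participants allocated × 12).
- Probiotic adherence = sachets taken / sachets scheduled, which is 28 per participant if one is scheduled daily for four weeks.

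The first costs one sentence and uses records already planned. The second needs a daily intake log or a count of returned sachets over the probiotic weeks, unless the full protocol already provides one. This is a small added burden on participants, since the training diary records exercise, the food diaries last 7 days each, and neither is described as covering all 28 days. Neither change affects the dose, the schedule or the 80% criteria.

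### The > 80% retention criterion is applied to complete adherence (all 12 runs and every measurement), so it does not measure staying in the trial and can fail when nobody has left

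*Protocol article*

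**What the plan says.** The Protocol article, Statistical analysis, introduces two rates with a shared purpose: "Attendance and retention rates will be assessed to calculate adherence".

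- **Attendance** is mean-based: "Attendance rate will be analysed by dividing the mean value for the number of participants present by the number of sessions offered". The section gives it no threshold.
- **Retention** is all-or-nothing: "The retention rate will be analysed by the percentage of participants completing all sessions of the endurance training (twelve in total"), followed by "shuttle run test (two in total), nutrition questionnaire (four in total), blood/saliva measurement (four in total) and stool diagnostics (four in total"). The sentence closes with "present in each step of the study".
- **Progression rule:** "A retention rate of > 80% will be considered as feasible to conduct a future randomised controlled trial".

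No allowance for a missed session or sample is stated. The count of twelve agrees with the Exercise intervention section ("The three 60-min running sessions per week" for four weeks). The Sample size section says that "a sample size of a minimum of 30 participants is required".

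**The concern.** Retention ordinarily means that a randomised participant is still in the study and supplies outcome data. The quantity defined here is full compliance with every scheduled item. A student who gives all four stool and blood/saliva samples, stays to the last visit and misses one of twelve runs is counted with those who left.

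Feasibility and practicality are the primary outcomes of this pilot, and the Discussion presents the progression criteria as a basis for the main trial. The retention rule is one of the few numerical criteria, beside the > 10% enrolment and > 80% recruitment rules in Participants and recruitment. A result below 80% could not show whether people withdrew, missed a single run or left out one food diary. Each would call for a different change to the main trial.

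**Working it through.** The > 80% figure is a chosen cut-off, so the plan has no calculated value to reproduce. The check is how strict the cut-off becomes under the stated definition.

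**Inputs from the Protocol article**
- Runs: 3 per week × 4 weeks = 12.
- All items: 12 + 2 + 4 + 4 + 4 = 26.
- Sample size: 30. Since 24/30 is exactly 80%, more than 80% means at least 25 of 30.

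**Assumptions (not in the document)**
- Mean attendance of 95% per item with no dropout, as an illustration.
- Correlation of absences within a participant: independence, then ICC up to 0.7 (beta-binomial).

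**Step 1. Per-item completion needed for 80% of participants to complete everything, if absences are independent:** p = 0.80^(1/k).

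| Component | k | p needed |
|---|---|---|
| Shuttle runs | 2 | 0.894 |
| Diaries, blood/saliva or stool (each) | 4 | 0.946 |
| Runs | 12 | 0.982 |
| All items | 26 | 0.991 |

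**Step 2. The same requirement when absences cluster:** mean completion at which the beta-binomial probability of completing all k items is 0.80.

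| ICC | 12 runs | 26 items |
|---|---|---|
| 0.1 | 97.2% | 98.2% |
| 0.3 | 95.3% | 96.5% |
| 0.5 | 92.9% | 94.3% |
| 0.7 | 89.6% | 91.0% |

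The arithmetic floor is just over 80%, reached only if all absences fall on the same few participants.

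**Step 3. Chance of meeting the rule at 95% mean attendance with no dropout:** q = probability of completing all k items, then P(Bin(30, q) ≥ 25). Under independence q = 0.95^12 = 0.540 and 0.95^26 = 0.264.

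| ICC | q, 12 runs | Pass, 12 runs | q, 26 items | Pass, 26 items |
|---|---|---|---|---|
| 0 | 0.540 | 0.08% | 0.264 | about 10^-10 |
| 0.1 | 0.668 | 3.7% | 0.528 | 0.05% |
| 0.3 | 0.788 | 37% | 0.727 | 13% |
| 0.5 | 0.855 | 74% | 0.823 | 56% |

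**Step 4. Higher attendance, independent absences.** On the 12 runs the chance of passing is 0.35 at 98% and 0.88 at 99%. On the 26 items it is 0.004 at 98%, 0.28 at 99% and 0.85 at 99.5%.

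**Step 5. Precision of the threshold.** The exact 95% confidence interval for 25/30 is 65% to 94%.

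**The case against.** A reader might infer that the rule demands 98–99% attendance and would fail any feasible trial. The document does not support that. The 98–99% figure needs independent absences, whereas missed sessions may well concentrate in a few people. The document gives neither a correlation nor an expected attendance, so 95% is only an illustration. With strong clustering, or with attendance near 99.5%, the rule can be met. Nor does the text say that a rate of 80% or less means not feasible.

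The closing words "present in each step of the study" also allow a rate per component. The measurements would then need only about 89% to 95% per item under independence, and the authors may already intend component-by-component reporting. This stands as a limit on the 26-item figures. It does not rescue the training component, which still requires all twelve runs.

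Full completion is also not irrelevant. The section says that both rates serve to calculate adherence, and Aims and objectives includes session frequency and participants' time commitment in the primary outcome. That justifies reporting full completion, but not calling it retention and attaching the only threshold in that section to it. The attendance rate, which would tolerate an occasional absence, has no threshold.

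**Conclusion.** The concern holds as a fault of definition and needs no assumption to establish: the > 80% rule is tied to complete adherence, and one missed run makes a participant not retained for training on either reading. Whether the rule covers one composite or five separate rates is not settled by the text.

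The rule is stricter than 80% retention, by an amount that depends on clustering: about 98.2% per run or 99.1% per item if absences are independent, falling to about 90% and 91% at ICC 0.7. At the assumed 95% attendance with no dropout, it fails almost surely under independence and still fails in about one case in four at ICC 0.5 on the runs alone (100% − 74% = 26%). It can therefore give a failing result when nobody has left, but it will not necessarily do so.

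**What to change.** Separate the two concepts and say to which the threshold applies.

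1. **Retention:** randomised participants who remain to the end and provide the stool and blood/saliva samples needed for the cross-over comparison (baseline and the end of both periods), divided by all randomised. The final sample alone would not be enough, because the comparison uses both periods. Apply > 80% to this rate and show its exact 95% confidence interval.
2. **Adherence:** report the mean attendance rate already planned, written as sessions attended over sessions offered, because the present wording divides a number of participants by a number of sessions. Add the share of participants attending a minimum number of sessions that the investigators fix in advance. The document gives no basis for a particular minimum.
3. **Measurements:** report completion of each type separately, with full completion of all items listed descriptively.

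The cost is a few sentences and no extra data. The criterion becomes less strict on training compliance, which the separate adherence figures then cover.

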## Methods

### Pilot trial design, study setting and ethics

This randomised controlled pilot cross-over trial is conducted at the German Sport University Cologne in cooperation with the MVZ Institute of Microecology GmbH. Data will be collected through bachelor endurance courses at the German Sport University Cologne (Cologne, Germany).

The study was approved by the Ethics Committee of the German Sport University Cologne (No. 136/2016). A schematic of the study design is given in more detail (see Additional file 1). To ensure all necessary aspects were addressed in the study protocol, the Standard Protocol Items: Recommendations for Interventional Trials (SPIRIT) checklist was adhered [37, 38] (Additional file 2).

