#### Nutritional data

Each participant will complete four detailed 7-day food diaries based on self-reported intake prior to the next faecal sample collection. A standardised protocol will be developed by a research dietitian supervisor. Subjects will maintain a habitual diet, such that potential gastrointestinal modifications can only be attributed to the intervention of sports or probiotics.

Nutritional quality and quantity of consumed foods and drinks as well as nutritional supplements will be recorded. A prepared protocol with instructions will help to guide the data recorded: breakfast, lunch, dinner, snacks, recipe information, preparation method (raw, steamed, boiled, fried, breaded, baked, with/without skin), fat/fructose content and food amount (gramme/millilitre).

Dietary data and personal data (gender, age, body height, body weight, body mass index) will be entered into the DGExpert software (version 1.8.9.0) to generate each subject’s energy and nutrient intake as well as respective reference values.

The following list of dietary parameters will be analysed each day in grammes/microgrammes/percentage:Energy/caloric intake (kilocalories, kilojoule)ProteinsFatsTotal fatty acidsPolyunsaturated fatty acidsMonounsaturated fatty acidsSaturated fatty acidsLinoleic acidLinolenic acidQuotient of linoleic acid to linolenic acidTotal carbohydratesAbsorbable carbohydratesFibresLactoseSucroseMonosaccharidesDisaccharidesTotal sugarAll vitamins and micronutrientsWaterAlcohol

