### Randomisation

Participants will be randomised in a 1:1 ratio and allocated to group one (endurance-probiotics) or group two (probiotics-endurance) via block randomisation by the study director [48]. Exclusion criteria will be injuries; diseases (e.g. inflammatory bowel diseases), an antibiotic therapy just before or during the intervention; and continuing gastrointestinal disturbances based on probiotic intake. Subjects who meet the inclusion criteria will obtain detailed information about the trial and will give written informed consent before starting the study.

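### The tests named for this two-sequence cross-over do not include a within-person exercise-minus-probiotic contrast or a period term

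*Protocol article*

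**What the plan says.** The section on trial design, setting and ethics fixes the design: "This randomised controlled pilot cross-over trial is conducted at the German Sport University Cologne". Under Randomisation, participants are "randomised in a 1:1 ratio and allocated to group one (endurance-probiotics) or group two (probiotics-endurance"), so each person is to receive both interventions in random order. Aims and objectives puts the efficacy question as endurance training compared with the probiotic, and lists a reliable estimate for sample size calculation among the primary outcomes. The Sample size section states that "a sample size of a minimum of 30 participants is required in order to provide a pooled standard deviation".

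The Statistical analysis section names three kinds of comparative analysis:

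- Depending on normality, "parametric or non-parametric (e.g. unpaired *t* test/Mann-Whitney *U* test) tests will be carried out". This is firm in wording, but the test is an example and the variable it applies to is not given.
- "a paired *t* test/Wilcoxon test might be computed for the longitudinal comparison (T0–T3"). This is optional.
- "Multivariate analyses with linear or logistic regressions might be performed to explore potential effects of the intervention and further potential covariates and cofactors". This is also optional, and no participant, period or sequence term is mentioned.

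The same section calls hypothesis testing and regression entirely exploratory, and says the data will be used to estimate sample size and choose the outcome measure for the main study. On attribution, the Nutritional data section says that habitual diet will be maintained so that "potential gastrointestinal modifications can only be attributed to the intervention of sports or probiotics".

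**The concern.** In a two-sequence cross-over, randomisation supports one main contrast: exercise minus probiotic within the same person, adjusted for period. The tests that the article names are, read plainly, those of a parallel-group or before–after study.

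An unpaired test on raw values gives up the precision for which a cross-over is normally chosen. A paired before–after test keeps within-person data but has no concurrent untreated group, so term-time drift, continued university courses and repeated measurement are all counted as effect. If the paired test compares T3 with T0, everyone has had both interventions by then and the change reflects both.

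At stake are the effect estimates, confidence intervals and standard deviations that the pilot is meant to pass to the main trial.

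**Working it through.** **The plan's own figure.** The sample size of 30 cannot be reproduced, because the article gives no SD, effect size, power or target precision. For an SD pooled over two groups (28 degrees of freedom), the chi-square 95% limits are 0.79 to 1.35 times the estimate. With no target stated, this neither confirms nor refutes 30.

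**Inputs.** From the article: at least 30 participants, 1:1 allocation (so 15 per sequence) and significance at p < 0.05, taken as two-sided. Assumed for illustration: total SD 1, within-person correlation rho from 0.3 to 0.7, a true difference of 0.5 SD, and the drift values shown below.

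**Unpaired test on period 1 against the cross-over contrast.**

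- Period 1 only, 15 v 15: variance = 2/15, SE = 0.365.
- Cross-over contrast (half the between-sequence difference in mean period differences): variance = 2(1 − rho)/30.
- Ratio = (2/15) ÷ (2(1 − rho)/30) = 2/(1 − rho).

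| rho | SE, period 1 | SE, cross-over | variance ratio | power, period 1 | power, cross-over |
|---|---|---|---|---|---|
| 0.3 | 0.365 | 0.216 | 2.9 | 26% | 61% |
| 0.5 | 0.365 | 0.183 | 4.0 | 26% | 75% |
| 0.7 | 0.365 | 0.141 | 6.7 | 26% | 93% |

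Powers are for t tests with 28 degrees of freedom. A normal approximation gives 28% for period 1 and 78% for the cross-over contrast at rho 0.5.

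**Unpaired test on both periods as if independent (30 v 30).** The nominal variance is 2/30 and the true variance 2(1 − rho)/30. At rho 0.5 the nominal SE is √2 times too large, and the true type I error is about 0.6% by normal approximation instead of 5%.

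**Unpaired test on period differences.** This is the standard cross-over test. In simulation at rho 0.6 it had 5% type I error and 84% power for 0.5 SD, and stayed unbiased under a period effect.

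**Paired before–after test, n = 30.** The standardised change is drift/√(2(1 − rho)). A drift of 0.3 SD with no intervention effect is declared significant in 36% of trials at rho 0.5 and 54% at rho 0.7.

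**Paired test of T3 against T0 with the sequences combined**, if that is what is meant (simulation, rho 0.6):

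- both effects 0.5 SD, so no difference between treatments: rejects in 84%;
- effects +0.5 and −0.5 SD, so a difference of 1 SD: rejects in 3%;
- exercise 0.5, probiotic 0: mean change 0.25, which is neither effect.

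**Consequence for the main trial.** For 0.5 SD and 80% power, a parallel-group trial needs 64 per arm, 128 in all. A cross-over needs about 34 at rho 0.5 or 21 at rho 0.7. Which SD is reported therefore matters once the main design is chosen.

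**The case against.** Several stronger readings are tempting, and the article does not support them.

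- A reader might infer that the paired test combines the sequences and compares only T3 with T0. The article says only that it "might be computed for the longitudinal comparison (T0–T3"). With four stool and four blood/saliva measurements planned, that label may name the visit series. Tests between successive visits or within a sequence need not mix the two interventions in the first treatment period, though they would still confound treatment with time.
- A reader might infer that the unpaired test necessarily throws away within-person information. It is an example on an unnamed variable; applied to period differences it would lose nothing. The optional paired test also uses within-person data.
- A reader might infer that the efficacy question cannot be answered by the named tests. A period-1 comparison of the randomised groups answers it without bias and free of carry-over. The loss is precision.
- A reader might infer that the main trial would inherit the wrong SD. The article calls it a randomised controlled trial and does not say it will be a cross-over. For a parallel-group trial the between-person SD is the relevant one.

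It can also be said that model terms are often left to an analysis plan, that all testing is exploratory, and that the progression thresholds concern recruitment and retention. These points lower the severity. They do not remove the issue: the article does name tests, what it names does not state the contrast its design was built for, and the resulting estimates feed a primary outcome.

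**Conclusion.** The point holds in limited form. For a two-sequence cross-over comparing exercise with probiotic, the Statistical analysis section names an unpaired test on an unspecified variable, an optional paired T0–T3 test and optional regressions, with no within-person treatment contrast and no period term. On ordinary use with raw values, the period-1 variance is 4 times that of the cross-over contrast at rho 0.5 (2.9 to 6.7 times for rho 0.3 to 0.7), and power for 0.5 SD is 26% against 75%. Any before–after test is uncontrolled for time, so the attribution sentence in the Nutritional data section claims more than the design can deliver; constant diet removes only one alternative explanation.

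The correlation, effect size and drift are illustrative and not taken from the article. The cross-over gain rests on no differential carry-over. As testing is exploratory and the feasibility criteria do not depend on it, this should be fixed but is not critical.

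**What to change.** For each parameter, estimate exercise minus probiotic with a 95% CI by one of two routes:

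1. an unpaired t or rank test on each person's period difference, compared between sequences (the mean difference is halved to give the effect); or
2. a mixed model with treatment, period and sequence as fixed effects and participant as random effect.

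State the assumption of no differential carry-over and show the period-1 comparison as a sensitivity analysis. The assumption matters. If half of a 0.5 SD exercise effect persisted into the next period and the probiotic had none, the mean period differences would be 0.5 − 0.25 = 0.25 and 0 − 0.5 = −0.5. The estimate would then be (0.25 + 0.5)/2 = 0.375 instead of 0.5.

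Report both the within-person and the between-person SD, so that the main trial can be sized for either design. Present T0–T3 changes as uncontrolled description, saying which visits are compared and whether by sequence. Soften the attribution sentence in the Nutritional data section.

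The cost is a few sentences. No new data are needed, and the planned software (SPSS 25) fits the model.
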